### Therapist Training

The I-TOPS intervention and the wellness treatment will be delivered by psychologists with expertise in psychotherapy. To ensure fidelity and quality assurance, all psychologists will receive training in recruitment strategies, interviewing techniques, questionnaire administration, and delivery of the I-TOPS and wellness interventions before beginning the program implementation; instructions for delivering each session are detailed in a treatment manual written by the TOPS program developer [name] and her research staff.

### Treatment Fidelity

In relation to the I-TOPS intervention, psychologists will receive weekly supervision from a qualified psychotherapist with a master’s in clinical psychology, a specialization in cognitive behavioral psychotherapy, and qualification in clinical neuropsychology to ensure treatment fidelity and quality assurance.

With respect to the wellness intervention, a supervising psychotherapist will conduct a random review of the sessions conducted by the psychologists every 2 weeks to ensure fidelity. The main topic of discussion will be how to focus on the ABI consequences without directly teaching problem-solving strategies to manage those consequences.

### Data Collection

Following completion of the consent process, sociodemographic information (eg, age, sex, and socioeconomic status); details of past medical history; concurrent medication; the adolescent’s age at the time of injury; and injury severity, measured using the Glasgow Coma Scale [61] will be collected from each patient’s referring physician. Family compositions will be collected from parents via telephone for outpatients or directly in the clinic for hospitalized patients who are close to discharge.

At baseline (T0), after treatment (T1), and at 6-month follow-up (T2), adolescents and parents will be asked to complete study outcome measures, including questionnaires on cognitive and behavioral functioning of adolescents, and the psychological well-being of parents and adolescents will undergo remote cognitive performance–based evaluations. Questionnaires will be sent to adolescents and families in a sealed envelope; after completing them, adolescents and parents will be required to return them to the research staff using an envelope with a postmark included in the sealed envelope within 2 weeks. To promote participant retention, support from a member of the research team could be given for questionnaire fulfillment, if needed. In addition, performance-based measures on adolescents’ cognitive functioning will be remotely administered, thus removing practical barriers to patient retention in the study, such as difficulties in transportation and reaching research centers.

### Feasibility Outcomes

Outcome measures to assess study feasibility will be taken and adapted from previous studies on telerehabilitation interventions for adolescents with ABI, with the aim to use a priori–defined criteria and allow comparisons [54,60]. These measures have been developed for a previous study [60] based on the relevant literature on pilot feasibility studies [62,63]. A total of 9 measures will be used: 4 to assess the feasibility of the I-TOPS or the wellness intervention (ie, accessibility, training adherence, technical smoothness, and training motivation) and 5 to evaluate the study design and procedures (ie, participation willingness, participation rates, assessment procedures, and assessment length and loss to follow-up).

With respect to the feasibility of the I-TOPS or the wellness intervention, the outcomes outlined in Textbox 2 will be considered.

In relation to the feasibility of study design and procedures, the outcomes outlined in Textbox 3 will be considered.

Outcomes to be considered regarding the feasibility of the Italian version of Teen Online Problem-Solving (I-TOPS) or wellness intervention.Accessibility: number and percentage of participants who ask for further instructions to understand training content and session-related tasks when at home. This criterion refers to understanding how to access the training, how to enter a session, how to perform and save exercises, and how to print specific materials. The criterion for success: 90% of families understand training content and session-related tasks when at home, after the explanation of sessions’ content and activities by the psychologist. For all families, the explanation of the content of sessions will be performed during each scheduled web-based meeting (ie, at the end of each session, the psychologist will briefly explain the content of the following one, also indicating to families the web-based activities they are expected to do for the next meeting), with instructions repeated if a family asks for further clarification. If ≥3 explanations are needed, requiring other remote calls, the criterion will be considered to not have been satisfied. The criterion for success was 100% in the paper presenting the original version of the feasibility criteria [60] and in a previous study of our research group [54], both focusing on remote cognitive interventions having a drill-based format. However, for this study, it was reduced to 90%, given the complexity and multiple requirements of navigating and completing content in the I-TOPS intervention.Training adherence: number and percentage of the 10 core sessions completed during the scheduled training period (ie, expected time for completion of the 10 core sessions is 5 months) by each patient, including dropouts. No data on the number of log-ins or average session length will be recorded, as, for both treatments, these data do not provide significant information on better training use and are not considered to be associated with improving target abilities. The criterion for success: average 80% of treatment core sessions is completed after 5 months by each treatment group; the remaining 20% (ie, 2 core sessions) should be completed in a maximum 1 further month (ie, 2 extra weeks for each session). To be adherent, participants needing an additional month to complete the training need to have agreed in advance with the psychologist to postpone sessions due to valid reasons (such as holidays or other family plans). The average completion rate per treatment group in the scheduled time frame, calculated as the sum of the percentage of sessions completed by each participant divided per the total number of participants, is considered.Technical smoothness: number and percentage of participants who encounter technical issues with the training material (eg, the platform does not work) that persist for 2 or more weeks, thereby generating a training interruption and possibly influencing total training duration. The criterion for success: all participants will be able to perform the training without technical issues; dropouts are included in the calculation, considering only sessions performed.Training satisfaction: training satisfaction will be assessed through a satisfaction questionnaire created ad hoc for the original Teen Online Problem-Solving program and already used in previous studies on its feasibility (Multimedia Appendix 1) [46,47]. The questionnaire assesses perceived helpfulness and usability of the program and improvements as a result of treatment, and for this study, it was translated into the Italian language. Item responses include 1 (ie, strongly disagree), 2 (ie, disagree), 3 (ie, agree), and 4 (ie, strongly agree) on a Likert scale. In particular, 5 items pertain to perceived changes in one’s problem-solving abilities and psychological wellness, 10 items pertain to satisfaction with the overall program (ie, program helpfulness and enjoyment and relevance of contents), and 2 items focus on the website ease of use. The questionnaire generates a total score, with higher scores indicating greater perceived satisfaction. A total score of ≥57 reflects a positive outcome in terms of satisfaction. The criterion for success: 80% of participants have a neutral or positive global score on the questionnaire.

Outcomes to be considered in relation to the feasibility of the study design and procedures.Willingness to participate: number of participants who accept to partake in the study among those who were contacted for study enrollment. The criterion for success: 75% of eligible participants agree to take part in the study; the criterion is considered on the whole group, as referred to prerandomization data.Participation rates: number and percentage of enrolled participants who complete ≥1 session of the interventions, not abandoning the study after baseline measurements and before the start of the training. The criterion for success: 80% of participants who agreed to partake actually participate in the study.Assessment procedures: number and percentage of participants for whom outcome data are collected without any problems (eg, missing data and technical issues of assessment tools) on the 3 assessment time points (ie, baseline [T0], after treatment [T1], and 6-month follow-up [T2]). The criterion for success: 90% of the outcome measures for each participant are collected at each time point.Assessment timescale: number of participants whose follow-up data are collected within a week after training completion, for posttraining assessment, and within 2 weeks after the 6-month period from training end, for follow-up evaluation. The criterion for success: for all participants, the interval between training end and immediate posttraining evaluation is ≤7 days; for the 6-month follow-up, the assessment is performed in a range of 0 to 14 days from the first day of the 6 months subsequent to training end. This criterion is calculated only for participants performing posttraining and follow-up evaluations, excluding dropouts.Loss to follow-up: number of patients who fail to complete all outcome measures at posttraining assessment and 6-month follow-up. The criterion for success: less than 20% of participants enrolled fail to complete all outcome measures on both posttraining assessment and 6-month follow-up. This criterion does not refer to the presence of evaluations with missing data for each participant, for which the criterion “assessment procedures” already provides such information.

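### The training-satisfaction criterion cannot be applied as written: the 57-point cut does not fit the 17 items described, and the 'neutral' band has no score range

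*Protocol article*

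**What the plan says.** Training satisfaction is one of four outcomes on the feasibility of the intervention (Protocol article, Feasibility Outcomes, Textbox 2). The text gives these elements:

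- Response scale: "Item responses include 1 (ie, strongly disagree), 2 (ie, disagree), 3 (ie, agree), and 4 (ie, strongly agree) on a Likert scale".
- Content, in three groups: "5 items pertain to perceived changes in one’s problem-solving abilities and psychological wellness"; "10 items pertain to satisfaction with the overall program"; and "2 items focus on the website ease of use".
- Scoring: "The questionnaire generates a total score, with higher scores indicating greater perceived satisfaction".
- The only cut: "A total score of ≥57 reflects a positive outcome in terms of satisfaction".
- The success rule: "80% of participants have a neutral or positive global score on the questionnaire".

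The questionnaire itself is in Multimedia Appendix 1, which is not shown. The introduction to Feasibility Outcomes says that the measures were adapted from earlier studies "with the aim to use a priori–defined criteria and allow comparisons". The Results section says that the last patient was evaluated in February 2023 and that the feasibility analysis will follow publication of the protocol.

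**The concern.** Two things do not fit together.

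First, the cut and the instrument as described do not match. A threshold for a positive outcome would normally be met by someone who endorses every statement. On the items listed, it is not.

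Second, the success rule counts a neutral total as a success but never says where neutral begins. The response options do not supply an answer, because they pass directly from disagree to agree.

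What is at stake is a stated pass/fail verdict on one feasibility outcome. The scores have already been collected, so any lower bound set now is set after the data exist. A criterion meant to be fixed in advance would then depend on a later choice.

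A smaller matter belongs with this. The satisfaction criterion does not say whether people who left the study count in the denominator, although several neighbouring criteria do say so.

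**Working it through.** **Inputs** (all from Textbox 2 unless stated): item groups of 5, 10 and 2; item scores 1, 2, 3, 4; positive cut 57; success share 80%. From the Abstract (Results): 42 randomised; 34 completed the intervention and the post-treatment evaluation.

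**Step 1. The plan's own figure.** The article gives no derivation of 57, so it can only be tested against the items described.

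- Items: 5 + 10 + 2 = 17
- Minimum total: 17 × 1 = 17
- Maximum total: 17 × 4 = 68
- Scale midpoint: 17 × 2.5 = 42.5
- Every item answered agree: 17 × 3 = 51
- Shortfall against the cut: 57 − 51 = 6
- Mean item score needed to reach 57: 57 / 17 = 3.35
- 57 as a share of the maximum: 57 / 68 = 83.8%

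If no item is scored below 3, reaching 57 takes at least 6 answers of strongly agree with the other 11 at agree: 6 × 4 + 11 × 3 = 57. The cut is attainable, but all-agree does not attain it.

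**Step 2. The item count that 57 would fit.** All-agree equals 57 when 3k = 57, so k = 19.

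| Items | Range | All agree | Reaches 57? |
|---|---|---|---|
| 17 (as described) | 17–68 | 51 | no |
| 18 | 18–72 | 54 | no |
| 19 | 19–76 | 57 | yes, exactly |
| 20 | 20–80 | 60 | yes |

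The exact match is at 19 items, two more than described.

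**Step 3. Can the success rule be applied?** A total of 57 or more is positive and counts. A total below 57 counts only if it is neutral, and neutral has no range in the text. So totals from 17 to 56 cannot be classified. Two illustrative bounds on 17 items show that the choice matters: the scale midpoint (42.5, so totals from 43) and all-agree (51). A participant scoring 45 passes under the first and not under the second. Neither bound is in the document.

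**Step 4. The denominator.** The neighbouring criteria state theirs: training adherence and technical smoothness include dropouts, assessment timescale excludes them, and loss to follow-up refers to those enrolled. Satisfaction is silent. The pooled counts needed for 80% are:

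- Of 34 completers: 0.80 × 34 = 27.2, so 28 participants
- Of 42 randomised: 0.80 × 42 = 33.6, so 34 participants

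This contrast is an upper illustration. It assumes one questionnaire per participant and that none of the 42 − 34 = 8 non-completers returned one. The article says neither.

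**The case against.** **The appendix may resolve it.** The article never states a total of 17 items. It describes three groups, and the questionnaire is in an appendix not shown here. That appendix may contain more items, or scoring bands that include neutral. This stands as a limit on what can be concluded. A reader might infer that the cut is simply wrong, or that the questionnaire certainly has 19 items, and the document supports neither reading. If the appendix does list more items, the description in the main text is incomplete and still needs correcting.

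**A strict cut is not in itself an error.** On 17 items, 57 is inside the range and reachable, and nothing says that agreeing throughout must count as positive. A demanding positive band with a neutral band below it is coherent, and a total score can have a neutral band even when single items have no neutral option. This is fair, but such a scheme needs the lower edge of the neutral band, and the text does not give it.

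**All-agree does not necessarily fail.** A reader might infer that a respondent who agrees with everything fails the success criterion. That goes too far: 51 misses the positive cut but could be neutral.

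**The denominator is detail that an article may omit.** This is partly right, and the silence alone would be minor. It is raised because the article states the denominator for comparable criteria and because the rule is being clarified anyway.

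**The consequence is limited.** Satisfaction is one of nine feasibility measures, and the Data Analysis Plan promises frequencies and means, so readers will see results beside any cut. A reader might infer that the feasibility evidence as a whole is undermined, but the defect affects the verdict on this one outcome.

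**Conclusion.** The point holds in limited form. On the instrument as described, agreeing with all 17 items gives 51, six points below the only stated cut. That cut equals the all-agree total for 19 items, so either the cut or the item description may be misreported. The match suggests this without proving it, and the unseen appendix could settle it.

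Separately, and without depending on the item count, the success rule relies on a neutral band that has no range in the text. The 80% rule therefore cannot be applied to any participant scoring below 57. The size of the effect on the satisfaction rate cannot be computed, because it depends on the unstated bound and on scores that are not reported.

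The denominator could move the required count from 28 to 34, but only if no non-completer returned the questionnaire, which the document does not say.

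This is a descriptive feasibility outcome and the efficacy analysis is untouched. It should still be corrected, because the article presents these criteria as fixed in advance and the analysis was still to be done when it was written.

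**What to change.** Before the satisfaction scores are examined:

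1. Check the item count and the 57 cut against the questionnaire in Multimedia Appendix 1, and correct whichever is wrong.
2. State one numeric lower bound for a total that counts as success, and keep the rule that 80% of participants must reach it. One possible form is a mean item score of at least 3, that is 51 on 17 items or 57 on 19. If a neutral band is kept, give its range.
3. State which denominator decides the criterion. Report, by arm, the proportion reaching the bound among those who returned the questionnaire and the same count as a share of all randomised. The second figure shows how much non-response matters and need not treat non-responders as dissatisfied.
4. Record the date of the clarification and that it was made before scoring.

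The cost is a few sentences and one extra column in a table. The reported satisfaction rate may change. If the bound differs from the one used in the earlier studies of the programme, that should be noted so that comparisons stay interpretable.

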## Methods

### Trial Design

We will conduct a single-center, 2-arm, parallel-group RCT. The trial will apply a pre-post design, with a baseline preintervention assessment (T0), a postintervention assessment immediately after the 6-month intervention period (T1), and a long-term follow-up assessment conducted 6 months after the end of the intervention (T2). Participants will be randomly assigned to groups in a 1:1 ratio to receive the I-TOPS or the wellness intervention. The wellness intervention presents the same structure as the I-TOPS intervention but omits contents related to problem-solving. No change to the I-TOPS or wellness intervention content will be made during the trial; therefore, both interventions will be delivered in their initial Italian version. Eventual failures or system downtimes will be recorded and considered for the evaluation of the feasibility of the training, but no changes in functionality will be made. The trial was registered on ClinicalTrials.gov (NCT05169788) on December 23, 2021.

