### Efficacy Outcomes

A total of 9 outcome measures will be used to test preliminary evidence of training efficacy. Specifically, 7 self-assessed outcome measures (ie, 5 questionnaires for parents and 2 questionnaires for adolescents), 2 performance-based tasks assessing social cognition taken from a standardized neuropsychological battery, and a virtual reality–based assessment of everyday setting EF will be used. Questionnaires will be sent to patients and families in a sealed envelope; after completing them, participants will be required to return them to the research staff using an envelope with a postmark included in the sealed envelope within 2 weeks. The performance-based subtests assessing social cognition and the virtual reality–based assessment will be administered remotely using the Google Meet videoconference platform.

A detailed description of outcome measures is provided in Textbox 4. The sample of this study will include adolescents aged 11 to 19 years, but some measures and questionnaires have been standardized for populations having a lower maximum age range; however, they will be adopted for this study as no other measures with the same characteristics are available in the Italian language. The individual measures affected by this problem are clearly described in Textbox 4.

All outcome measures will be administered at T0 (ie, preintervention assessment), T1 (ie, immediately after the 6-month intervention), and T2 (ie, 6 months after the end of the intervention).

For the questionnaire outcomes, approaches to missing individual items will follow the guidelines for missing item procedures indicated in the manual for each questionnaire. If no guidelines for individual missing items are available, the mean of the completed items will be used to replace missing items if ≤10% are missing.

A summary of outcome measures to test training efficacy is presented in Textbox 5.

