## Results

After the approval of the ethics committee, the study started on February 26, 2021, and ended on February 28, 2023. Recruitment started on December 27, 2021, and ended on February 25, 2022. The last patient evaluation was performed on February 22, 2023. A secular event, namely the COVID-19 emergency, fell into the first part of the study period, which could have increased the interest of adolescents and families in participating in a remotely delivered treatment. However, due to the need of the target population to receive neurocognitive treatment in the chronic phase, we consider this fact marginal and not influencing the adherence rate. At study protocol submission in *JMIR Research Protocols*, the study has been concluded; the expected 42 participants were randomly assigned into the 2 treatment groups, and 34 (81%) of them concluded the assigned intervention and underwent posttraining and 6-month follow-up evaluations. The total attrition rate was 19% (8/42).

Figure 1 depicts the CONSORT (Consolidated Standards of Reporting Trials) flow diagram.

After the publication of the protocol, data analysis to test feasibility and efficacy will be performed, and final results are expected to be published in the form of a paper in a relevant scientific journal in 2025. In this paper, demographics associated with digital divide issues such as age, education, gender, family socioeconomic status, and computer or internet literacy will be reported.

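### The on-time criterion for the 6-month follow-up starts its 0-14 day window at the wrong end of the 6 months, contradicting the measure it scores and the trial's own definition of T2

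*Protocol article*

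**What the plan says.** The Assessment timescale entry (Protocol article, Feasibility Outcomes, Textbox 3) has two parts.

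- **Measure.** It counts participants whose follow-up data are collected "within 2 weeks after the 6-month period from training end, for follow-up evaluation".
- **Success criterion.** For T1, "the interval between training end and immediate posttraining evaluation is ≤7 days". For T2, "the assessment is performed in a range of 0 to 14 days from the first day of the 6 months subsequent to training end". Both limits must be met by all participants, and the denominator is restricted: "This criterion is calculated only for participants performing posttraining and follow-up evaluations, excluding dropouts".

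Elsewhere the timing of T2 is consistent. Trial Design has "a long-term follow-up assessment conducted 6 months after the end of the intervention (T2"), and Efficacy Outcomes has "T2 (ie, 6 months after the end of the intervention").

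The Results section gives the calendar: "Recruitment started on December 27, 2021, and ended on February 25, 2022. The last patient evaluation was performed on February 22, 2023". It also says that the study was over when the protocol was submitted and that the analysis would follow publication.

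**The concern.** The measure and the success criterion describe the same visit but start the clock at different points. The measure starts when the 6 months are over. The criterion starts on the first day of those 6 months, which is when training ends.

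Feasibility is the first of the trial's two objectives, and the article presents its nine criteria as fixed in advance so that results can be compared with earlier studies. This criterion has a 100% threshold, so a single visit decides it. If its wording supports readings that lead to opposite results, someone must choose a reading at the scoring stage. By then the visit dates are on file, because the visits had been made before the protocol was published. Criteria set in advance are meant to rule that choice out.

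**Working it through.** No figure in the plan needs reproducing. The check compares windows and dates.

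**Inputs**
- T1 limit: 7 days or less after training end (Textbox 3).
- T2 window: 14 days wide, with two different starting points (Textbox 3).
- T2 target: 6 months after the intervention ends (Trial Design; Efficacy Outcomes). Six calendar months are 181 to 184 days for training ending between May and September 2022.
- T2 visits made: 31 according to the Abstract. The Results section can be read as 34; nothing below depends on which is right.

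**Step 1. The windows side by side, in days after training end**

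| Reading | Window | Does a visit at exactly 6 months pass? |
|---|---|---|
| Measure | opens 181-184, closes 195-198 (opening + 14) | Yes |
| Criterion, literal | 0 to 14, or 1 to 15 if counted from day 1 | No |
| Criterion, as first day of the sixth month | opens at about 5 months, closes 14 days later | No |

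**Step 2. Distance between the literal window and a correct visit.** Smallest gap: 181 − 15 = 166 days. Largest: 184 − 14 = 170 days. The windows do not overlap. The T1 range of 0-7 days lies wholly inside the literal T2 range of 0-14.

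**Step 3. The sixth-month reading.** A month has 28 to 31 days. The window would therefore close 28 − 14 = 14 to 31 − 14 = 17 days before the 6 months are complete. A visit about a month early passes and a punctual one fails.

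**Step 4. Effect on the result.** If every T2 visit made was held at 6 months, the literal criterion scores 0 of 31, the sixth-month reading also scores 0 of 31, and the measure's window scores 31 of 31. The threshold is 100%.

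**Step 5. Does the calendar show mistimed visits?** From 25 Feb 2022 (last recruitment) to 22 Feb 2023 (last evaluation) is 362 days. Trial Design gives the intervention as 6 months ("a postintervention assessment immediately after the 6-month intervention period (T1")); the I-TOPS section expects the ten core sessions to take 5 months, and about 6 with supplemental sessions. For a participant who started on the last recruitment day:

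| Training length | 6-month point | Days left before last evaluation | Days left after the full 14-day window |
|---|---|---|---|
| 5 months | 25 Jan 2023 | 28 | 28 − 14 = 14 |
| 5.5 months | 9 Feb 2023 | 13 | 13 − 14 = −1 |
| 6 months | 25 Feb 2023 | −3 | −3 − 14 = −17 |

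For a participant who started on the first recruitment day, 27 Dec 2021, the margin before the last evaluation is 57 days even with 6 months of training. If the recruitment dates are consent dates, the time for baseline assessment and randomization shortens all of these margins. The schedule is therefore tight for late recruits who took the full 6 months, and not otherwise. Individual dates of training start, training end and T2 are not given.

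**The case against.** The best defence is that nobody would score the sentence literally. The correct window stands in the same entry, the criterion names the 6-month follow-up, and T1 has its own 7-day limit. A T2 window overlapping T1 makes no sense, so a careful reader would use the measure. This stands as to intent: it is a wording error with a recoverable meaning. It does not make the criterion usable as written, since the criterion is the part that decides success.

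A reader might also infer three stronger things, and the documents support none of them.

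- **That some T2 visits were early, or impossible for late recruits.** The 362 days against about 365 is correct arithmetic, but it bites only with 6 months of training and a start in the last days of recruitment. The article does not say how long training took, whether the latest recruits stayed in, or what event recruitment refers to. The date of 22 Feb 2023 is only when the last evaluation took place; the study ended on 28 Feb 2023, 3 days after the latest 6-month point in the table. Any count of affected participants would rest on assumed training length, baseline delay and accrual pattern.
- **That the criterion confuses visits falling due after closure with families who left.** It excludes dropouts. Missed visits belong to the separate Loss to follow-up measure.
- **That a mistimed window distorts the efficacy results.** The Data Analysis Plan includes all randomized adolescents and treats time as a three-level factor. The feasibility criterion does not decide which visits enter that model.

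**Conclusion.** The success criterion for T2 timing is wrong as written. It contradicts the measure in its own entry and the definition of T2 in two other sections. Taken literally, it fails every correctly timed visit by 166-170 days; taken as the sixth month, it passes visits about a month early and fails punctual ones. This finding rests on the wording and on the length of six calendar months, and on no assumption about how the trial ran.

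The consequence is confined to one of nine feasibility criteria. The efficacy model and the loss-to-follow-up measure are unaffected. The calendar gives a reason to score this criterion from actual dates; it is not evidence that any visit was mistimed.

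**What to change.** Reconcile the two sentences before the criterion is scored. State the T2 window as 0 to 14 days after completion of the 6 months following training end, which is what the measure already says. Apply it to each participant's actual dates, and report any T2 visit held before 6 months as outside the window. A short table of days from training end to T1 and to T2, by arm, would let readers verify the result.

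The cost is one sentence and one table, using training-end and visit dates that scoring this criterion needs in any case. No visit, treatment or analysis model changes, and the analysis was still to come when the protocol was published. The on-time percentage may turn out less favourable than under a looser reading.
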